#### Statistical Analysis

This study will evaluate weather MI-E with HFO is significantly superior to MI-E without HFO in terms of the change in SpO_2_ as the primary endpoint of this study. If the protocol treatment with HFO is found to be statistically significantly superior to the treatment without HFO, the study will conclude that the addition of HFO to MI-E is more efficacious than not adding HFO.

The ΔSpO_2_ is calculated by subtracting the SpO_2_ value of pre-MI-E from the SpO_2_ value of post-MI-E. For every subject, the average of ΔSpO_2_ with or without HFO will be obtained. Then, a statistical analysis will be performed using a paired *t* test for the average ΔSpO_2_ values. The hypothesis testing will use a 2-sided significance level of 5%, with a calculation of the 2-sided 95% CI. The change in heart rate (ΔHR) as the secondary efficacy endpoint will be examined in the same way.

The safety endpoint of this study is the frequency of adverse events and complications. A summary table will be prepared for this endpoint. For estimation of the proportion, the exact 2-sided 95% CI for binomial distribution will be calculated by group. As necessary, Fisher exact test will be used for intergroup comparison. The final analysis will be performed after data from the subjects have been obtained and locked after the end of the follow-up period. The full analysis dataset and safety analysis dataset will consist of all subjects enrolled in this study, who performed at least one protocol treatment and for whom efficacy data are available.

The statistical analysis will be performed using GraphPad PRISM 7.02 (GraphPad Software).

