#### Description of the Processes and Interventions

The principal subinvestigator will obtain written informed assent or consent from patients or from their parents. After informed consent is obtained, the principal investigator or subinvestigator will determine the subject’s eligibility for enrollment. Enrollment should be done within 2 days after obtaining written consent, and protocol treatment should be started within 1 day after enrollment.

For the patients currently using MI-E, they will continue to use it with their existing settings. For new MI-E users, the setting described above will be used.

The following subject information will be recorded in the case report form (CRF) at the time of obtaining informed consent: date of informed consent; subject identification code; and subject’s baseline characteristics, including sex, birth date, height, body weight, medical history, concurrent diseases, and original setting of MI-E.

HFO will be added to MI-E in every subject on every other day, for 6 days. The addition of HFO on day 1 or day 2 will be determined in a random manner. When the subject is randomly selected to start the protocol with HFO on, the subject will receive MI-E with HFO treatment on days 1, 3, and 5 (Figure 1). If the subject is randomly selected to start the protocol with HFO off, they will receive MI-E with HFO on days 2, 4, and 6. The subject will thus be treated using MI-E with HFO for 3 days and without HFO for 3 days. During protocol treatment, the time for switching to HFO on and off has been set as 9 am.

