#### Criteria for Discontinuation

When continuation with the study is judged to be impossible for any of the following reasons, the principal investigator or subinvestigator will terminate the subject’s participation in the study and specify the date and time of discontinuation or dropout, reason for discontinuation, and clinical course in the medical records and CRF. The reasons for discontinuation include the following: when the subject or their parents request to withdraw from the study; when the subject’s respiratory status worsens and continuation of the study treatment is judged to be undesirable; when an adverse event, including pneumothorax, occurs and further continuation with the study is difficult; when the subject is discharged from the hospital; and when discontinuation from the study is appropriate for other reasons in the opinion of the principal investigator or subinvestigator.

When subjects who have already used MI-E have completed the protocol, MI-E will be set at the original setting. For subjects who commence use of MI-E for the first time in this study, MI-E will be set at a clinically favorable setting. HFO will be added if requested by the subject. For each subject, the observation period will end on the day when the subject visits the outpatient clinic of Kobe University Hospital for follow-up at 2 to 4 weeks after discharge.

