#### Secondary Outcomes

To evaluate the efficacy of the treatment, changes in heart rate will be obtained at the same time point used for SpO_2_. Additionally, the amount of mucus removed will be assessed subjectively, according to 3 grades (little, moderate, and abundant). As it was recommended by an external reviewer, peak cough flow was added to the secondary outcomes at the midpoint of the study. As safety end points, adverse events and the incidence of complications during the observation period will be obtained. The worst grade of the event will be considered the severity grade of each observed adverse event.

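### Fisher's exact test is named for comparing adverse events between HFO-on and HFO-off, although the same subjects supply both conditions

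*Protocol article*

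**What the plan says.** All references are to the protocol article.

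- **Design** (Description of the Processes and Interventions). "HFO will be added to MI-E in every subject on every other day, for 6 days". Only the starting condition is randomised: "The addition of HFO on day 1 or day 2 will be determined in a random manner". The result is that "The subject will thus be treated using MI-E with HFO for 3 days and without HFO for 3 days". The switch takes place at 9 am.
- **Efficacy** (Statistical Analysis). SpO2 changes are averaged per subject and condition, and the two sets of averages are compared by a paired *t* test; heart rate is handled in the same way.
- **Safety** (Statistical Analysis). A summary table is promised. On intervals, the plan says: "For estimation of the proportion, the exact 2-sided 95% CI for binomial distribution will be calculated by group". On a test between the two, it has only this conditional sentence: "As necessary, Fisher exact test will be used for intergroup comparison". The article does not define the groups.
- **Safety window** (Secondary Outcomes; Criteria for Discontinuation). "adverse events and the incidence of complications during the observation period will be obtained". That period ends at an outpatient visit 2 to 4 weeks after discharge. After the protocol days, "HFO will be added if requested by the subject".
- **Size** (Target Sample Size and Rationale). 5 subjects, with at least 45 sessions expected per condition.

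**The concern.** If the two groups are HFO-on and HFO-off, they are the same 5 people. The reference distribution of Fisher's test treats the two rows of the table as separate people, and it discards the information on who had an event under both conditions, one, or neither. The only separate sets of subjects in this design are the two starting sequences, and comparing those does not compare HFO with no HFO. On either reading, the named test does not answer the safety question.

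The section also disagrees with itself: it pairs the two conditions for SpO2 and heart rate and unpairs them for adverse events.

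A smaller matter follows from the safety window. Events after day 6 fall outside both protocol conditions, and any HFO use then follows the subject's request, not the allocation. A by-condition comparison needs a boundary that keeps such events out of it.

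At stake is the meaning of any safety p value that is reported. A reader could be shown a significant difference that the paired data do not support, or a non-significant result from a test whose real size is far below 5%.

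**Working it through.** The article gives no figure for the safety comparison, so there is none to reproduce.

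**Inputs.** n = 5 subjects, each in both conditions, and a two-sided 5% level (all from the article; the level is the one set for hypothesis testing in general). Event rate and within-subject correlation are not given; the values below are assumptions. Each subject counts once per condition.

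**Step 1. Tables that Fisher would call significant.** With 5 v 5, the two-sided p is twice the hypergeometric probability of the extreme table:

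- 5 v 0: 2 × 1/C(10,5) = 2/252 = 0.0079
- 4 v 0: 2 × C(5,4)/C(10,4) = 10/210 = 0.0476
- 5 v 1: 2 × C(5,1)/C(10,6) = 10/210 = 0.0476

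The next smallest p values are 0.1667 (3 v 0 and 5 v 2), so apart from mirror images only these three reach 5%.

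**Step 2. The same tables as pairs.** The margins fix the pairing in all three. 5 v 0 is five subjects with an event on HFO only. 4 v 0 is four such subjects and one with neither. 5 v 1 is four such subjects and one with both. Exact McNemar with k discordant pairs, all in one direction, gives p = 2 × 0.5^k.

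| HFO-on v HFO-off | Discordant pairs | Fisher p | Exact McNemar p |
|---|---|---|---|
| 5 v 0 | 5 | 0.0079 | 0.0625 |
| 4 v 0 | 4 | 0.0476 | 0.125 |
| 5 v 1 | 4 | 0.0476 | 0.125 |

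The verdict at 5% differs in every row. With 5 pairs the smallest attainable paired p is 0.0625; six one-way discordant pairs would be needed (2 × 0.5^6 = 0.031).

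**Step 3. True size of Fisher's test.** Under no difference, let q be the probability of an event on HFO only, equal to that of an event off HFO only. Summing the multinomial probabilities of the three tables and their mirror images:

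size = 2[q^5 + 5q^4(1 − 2q)] = 10q^4 − 18q^5

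With event rate p and ordinary correlation ρ between a subject's two outcomes, q = p(1 − p)(1 − ρ).

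- p = 0.4, ρ = 0: q = 0.24; size = 0.0332 − 0.0143 = 0.019.
- p = 0.4, latent Gaussian correlation 0.5: the probability of events under both conditions is 0.239, so q = 0.161; size = 0.0048.
- p = 0.5, ρ = −0.3, 0, 0.3, 0.6: q = 0.325, 0.25, 0.175, 0.10; size = 4.6%, 2.1%, 0.6%, 0.08%.
- p = 0.3, same correlations: size = 2.8%, 1.2%, 0.3%, 0.04%.

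The formula passes 5% only when q exceeds about 0.335, that is, when more than two thirds of subjects are expected to have an event under exactly one condition (2 × 0.335 = 0.67). That requires marked negative dependence: with p = 0.5 and latent correlation −0.9 the size is 0.077.

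**Step 4. Unit of analysis.** The sample-size section counts 3 sessions × 3 days × 5 subjects = 45 per condition. If sessions were the unit, 6/45 v 0/45 would give Fisher p = 0.026 even if all six events came from one subject. By subject, that is a single discordant pair (McNemar p = 1). The article does not say that sessions will be the unit; this shows why the subject should be.

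**Step 5. The intervals.** A separate exact interval for each condition needs independence between subjects within that condition, not between conditions. With n = 5, 0/5 gives 0 to 52.2% and 1/5 gives 0.5% to 71.6%. Each is valid on its own.

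**The case against.** The defence has real substance. Safety is a secondary outcome, the test is to be used only if needed, the sole decision rule concerns SpO2, and the article calls the study preliminary. A descriptive summary table is already promised. The paired replacement cannot reject at 5% with 5 subjects, so no formal safety conclusion would improve. All of this stands and sets the weight of the point. It does not rescue the test: making an analysis optional does not make it valid, and since the article names the method, the choice cannot be put down to an analysis plan that is not shown.

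Three stronger readings are tempting, and the documents do not support them.

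- *The by-group binomial intervals are invalid too.* They are not, provided each subject counts once per condition (step 5). The error would lie only in comparing the two intervals as if they came from independent samples, or in using clustered sessions as the denominator.
- *Fisher's test will manufacture false signals of harm.* The three tables show conflicting p values, not an inflated error rate. One patient in one infection episode more plausibly gives positive dependence, and the test is then conservative. Size above 5% needs strong negative dependence, which nothing in the article suggests.
- *Events after day 6 are forced into a group.* No passage does this. The article sets a long collection window and states no attribution rule, and a condensed article may leave such a rule to the full protocol. The boundary is worth stating, but its absence is not itself an error.

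**Conclusion.** The named test does not fit the design. Fisher's exact test assumes independent samples, HFO-on and HFO-off are the same 5 subjects, and the same section treats them as paired for efficacy.

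The consequence is a p value without its nominal meaning: true size about 0.02 at zero correlation and about 0.005 at latent correlation 0.5 (assumed event rate 0.4), and a 5% verdict that conflicts with exact McNemar in every table that Fisher would call significant. These figures assume 5 complete subjects, each counted once per condition. The size figures also rest on assumed event rates and correlations; the p values in the table do not.

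Severity is minor. The mismatch itself is certain, but neither the efficacy conclusion nor any stated decision rule depends on it.

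**What to change.** In Statistical Analysis:

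1. Replace Fisher's test with a descriptive within-subject table: event under both conditions, HFO-on only, HFO-off only, neither. Count each subject once per condition.
2. If a test is wanted, name exact McNemar and state that with 5 pairs its two-sided p cannot fall below 0.0625.
3. Keep the exact binomial interval for each condition, state that the subject is the unit, and say that the two intervals are not to be compared as if independent.
4. Restrict the by-condition comparison to events with onset on protocol days 1 to 6, assigned to the condition in force since the last 9 am switch. List later events separately, without a condition.

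The cost is a few sentences of wording, plus keeping the onset date and time with each event record. No new visit, measurement or subject is needed.

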### Outcomes

#### Primary Outcomes

Oxygenation change (SpO_2_) is the primary outcome in this study. Data will be obtained at every MI-E use during the study protocol. SpO_2_ values will be recorded at any point within 15 min before MI-E treatment and at 3 min after treatment.

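### The safety analysis set carries an efficacy-data condition, so a treated subject stopped by an early adverse event before any efficacy measure could drop out of the safety table

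*Protocol article*

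**What the plan says.** The Statistical Analysis section defines both analysis populations in one sentence. It begins "The full analysis dataset and safety analysis dataset will consist of all subjects enrolled in this study" and then limits these to subjects "who performed at least one protocol treatment and for whom efficacy data are available". Nothing in the sentence assigns one condition to one dataset and the other to the second, and no other section gives a separate safety population.

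On safety itself, the same section states: "The safety endpoint of this study is the frequency of adverse events and complications". Secondary Outcomes sets the collection window: "As safety end points, adverse events and the incidence of complications during the observation period will be obtained". The Criteria for Discontinuation section ends that period at the outpatient visit 2 to 4 weeks after discharge. The planned output is a summary table with exact binomial 95% intervals by group.

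On efficacy data, SpO2 is to be taken "at any point within 15 min before MI-E treatment and at 3 min after treatment", at every MI-E use. For heart rate, "changes in heart rate will be obtained at the same time point used for" SpO2. The three-grade mucus assessment has no stated time point. Peak cough flow was added partway through the study.

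**The concern.** A safety population should depend on exposure, not on whether an efficacy value was obtained. Adverse events are collected over the whole observation period and need no SpO2 or heart rate value, yet the rule lets the absence of such values decide whether a subject's events are tabulated.

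The condition is not neutral with respect to harm. The protocol expects that some subjects may stop "when an adverse event, including pneumothorax, occurs and further continuation with the study is difficult", and it also lists worsening respiratory status as a reason to stop. A subject stopped during or just after the first session is among the likeliest to have no post-session efficacy record. Safety is a stated objective, and with a target of 5 subjects a single exclusion removes 1/5 = 20% of the sample.

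**Working it through.** The protocol states no figure to reproduce here. The check compares the sections and then applies the protocol's own interval to a hypothetical case.

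**1. What is needed to enter the safety set.** Two conditions joined by *and*: at least one protocol treatment, and available efficacy data (Statistical Analysis). A treated subject with no efficacy data fails the second condition, whatever safety information exists.

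**2. What counts as efficacy data.** The term is not defined. The efficacy measures named under Primary and Secondary Outcomes are SpO2, heart rate, mucus grade and, later, peak cough flow. A change in SpO2 or heart rate needs the reading at 3 min after the session. The mucus grade is not tied to that time. Exclusion therefore requires every one of these to be missing, not SpO2 alone.

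**3. How often this could arise.** The device is used at least 3 times a day for 6 days, so 3 × 6 = 18 or more sessions per subject, with readings at each. Once one session yields an efficacy value, the subject is in the safety set and all later events count. In practice the exposure to the problem is the first session.

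**4. Direction of the effect.** Let x of n treated subjects have an event, and let one of those x be excluded. The reported proportion becomes (x − 1)/(n − 1). The difference is

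x/n − (x − 1)/(n − 1) = (n − x)/[n(n − 1)] ≥ 0,

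so losing a harmed subject never raises the proportion, and lowers it unless every subject had an event.

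**5. Size in a hypothetical case.** Inputs: n = 5 (Target Sample Size and Rationale), exact two-sided 95% interval (Statistical Analysis). Assumptions that are not in the protocol: exactly one subject has an event, in the first session, with no efficacy measure recorded, and the other four subjects all receive the same condition without an event.

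- All treated subjects counted: 1/5 = 20%. Lower limit 1 − 0.975^(1/5) = 0.0051. Upper limit is the p that solves (1 − p)^5 + 5p(1 − p)^4 = 0.025, which is 0.716. Interval 0.5% to 71.6%.
- Rule as written: 0/4 = 0%. Upper limit 1 − 0.025^(1/4) = 0.602. Interval 0% to 60.2%.

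**6. Which estimate this affects.** The intervals are calculated by group, read here as with and without HFO. A subject stopped in the first session has received one condition only. The contrast of 1/5 with 0/4 therefore applies to that condition. If the other condition is tabulated on those who received it, it has 4 subjects under either rule.

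**The case against.** The strongest reply is that the sequence is rare and partly conjectural. Readings are planned at every session, all efficacy measures must be missing, and nothing in the Criteria for Discontinuation section says that the 3-minute reading is skipped when a subject is stopped. The Discussion describes SpO2 monitoring as continuous and simple. A mucus grade could keep the subject in, and arguably so could the pre-session SpO2. All of this stands, and it limits how likely the loss is. It does not make the condition appropriate for a safety set.

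The event would also not vanish from the record. The date and reason for discontinuation and the clinical course go into the medical records and the case report form. That stands too: what is lost is the subject's place in the planned table and interval.

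Finally, the two intervals in the illustration overlap almost completely, safety is descriptive, and the article calls the study preliminary. Neither interval would support a different inference about the underlying rate. What does change is the reported count, from one event to none.

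A reader might infer more than the text supports in two ways. The first is that efficacy data exist only if SpO2 is read 3 minutes after a session. The rule says efficacy data without naming SpO2, and other measures are listed. The second is that any subject stopped on day 1 would be excluded for lacking both an HFO-on and an HFO-off average. The rule does not ask for paired data, so this cannot be read into it.

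**Conclusion.** The point holds as a badly fixed definition. As written, entry to the safety set depends on efficacy data, and a treated subject harmed before any efficacy measure is recorded would be left out of the planned safety table. This is a stated rule, not a detail left to an unseen analysis plan.

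Its practical weight is limited. The situation is likely to be uncommon, and the protocol gives no basis for a probability. The change from 20% to 0% is a hypothetical worst case resting on the assumptions listed in the check, and it concerns only the condition the subject received. A reader might conclude that the trial's adverse event rates are already biased downward. The documents do not support that, because the bias arises only if such a subject occurs.

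Severity: minor to moderate. The primary paired comparison is not affected.

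**What to change.** Split the sentence into two definitions. Safety analysis set: all enrolled subjects who received at least one protocol MI-E session, whether or not any efficacy data exist. Full analysis set: the same subjects, with the present condition that efficacy data are available.

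The cost is one sentence. No additional data are needed, because adverse events and reasons for discontinuation are already collected. No study procedure changes, and the primary analysis stays as planned. The change should be made before the data are locked for the final analysis.

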### Ethics

The study protocol was approved by the ethics committee of the Graduate School of Medicine, Kobe University (approval #290090).

## Results

A total of 2 subjects have already been recruited and enrolled in this study as of August 2018.

## Discussion

### Overview

This study will describe the efficacy of the addition of HFO to MI-E for the treatment of NMD patients with mild-to-moderate respiratory disease. A further goal is to provide the best selection of an airway clearance technique to prevent respiratory failure, especially when the patients have respiratory tract infection. The efficacy of HFO therapy in patients with NMDs has not been well studied to date. The efficacy of combined therapy including MI-E and HFO has been studied in patients with amyotrophic lateral sclerosis [20], but that study did not demonstrate an effect of increasing the peak cough flow. The peak cough flow is considered a key marker of the effect of airway clearance techniques. However, it is not recognized as a standard measurement, as the process, including device specification, instructions, and normal ranges, is not yet well-established [18]. In addition, it is difficult to test the peak cough flow on uncooperative pediatric patients or patients with advanced disease who only have a faint cough. In this study, we have set ΔSpO_2_ as the primary outcome for evaluating the effect of mucus removal by MI-E and HFO combination therapy. Continuous SpO_2_ monitoring is a simple noninvasive method of establishing the percentage of hemoglobin that is saturated with oxygen. It has been used for monitoring both the acute and chronic respiratory status of NMDs [14,21-23]. SpO_2_ has also been used as a measure of secretion clearance [24].

We recognized some limitations in this study. First, there is no previous report similar to this study. Therefore, it is difficult to estimate how much change will be obtained between HFO-on and HFO-off conditions and how many target samples will be sufficient to observe a statistically significant difference. Second, this is a single-center study, which limits the generalization of the findings. Third, the included subject group will be heterogenous, and the subjects are expected to demonstrate considerable variability in severity. Finally, as the optimal HFO setting in patients with NMDs has not been established [25], it is unclear if our appointed setting applied in this study will be appropriate for effective secretion removal.

